## Abstract

**Background:**

Nonpharmacological strategies have actually become more important in neonatal pain management during routinely applied minor painful procedures. However, commonly used nonpharmacological strategies are inferior to orally administered sweet solutions. Therefore, we will compare laser acupuncture, as a recent nonpharmacological method, with the standard care of oral glucose solution for pain prevention.

**Methods:**

Ninety-five healthy term neonates will be allocated into one of two groups. Before routine heel lance for metabolic screening, one group will receive laser acupuncture at acupuncture point Large Intestine 4 (LI 4) bilaterally for 60 seconds per point (acupuncture group) and the other will receive the standard care with orally administered glucose solution (glucose group). The complete procedure of blood sampling will be recorded on video, excluding the intervention before heel lance. A paediatric nurse, blinded with respect to the allocation, will evaluate these video recordings and determine the Premature Infant Pain Profile (PIPP) for each neonate. Primary outcome will be the mean difference in PIPP scores between groups.

**Discussion:**

This observer-blinded randomised controlled trial has been designed to explore potential advantages of laser acupuncture in the management of neonatal pain because more data are required to provide information about its efficacy and safety.

**Trial Registration:**

This trial is registered with DRKS00010122.

## 1. Background

In recent years, significant progress has occurred, in both the understanding of the physiology of neonatal pain and the efficacy of pharmacological and nonpharmacological interventions [1].

Neonates admitted to hospital are frequently subjected to acute pain, which causes short-term physiological instability and moreover long-term alterations in brain development, behaviour, and stress responses, potentially leading to a greater vulnerability to chronic pain [2–4]. As an example, a frequently used minor painful procedure in clinical routine in neonates is the heel lance for blood sampling.

The actual golden standard for pain prevention during minor painful interventions in preterm and term neonates is the treatment with orally administered sweet solutions. Recent systematic reviews have investigated the effectiveness of sucrose and glucose analgesia in neonates, concluding that both can reduce pain scores and crying duration during minor painful interventions [5, 6]. However, there is still a gap of knowledge regarding the long-term effects of sucrose [5].

Therefore, nonpharmacological strategies have actually become more important in neonatal pain management. Common nonpharmacological therapies are kangaroo care, swaddling, and nonnutritive sucking-related strategies; however, they all are inferior to orally administered sweet solutions but are considered due to their synergistic effects to achieve optimal analgesia [7, 8].

A new nonpharmacological and gentle method for pain prevention in neonates could be laser acupuncture treatment. Laser acupuncture in children and neonates is getting more and more popular, due to the fact that it is a noninvasive and simple-to-perform method. Moreover, the use of laser acupuncture performed within standardised guidelines and in compliance with all safety precautions seems to be safe [9].

Recently, there are only a few trials using acupuncture methods for pain reduction in neonates. Three trials investigated acupuncture in infantile colic and demonstrated significantly a reduction in the total duration of fussing and colicky crying [10–12]. Five other studies investigated acupuncture for pain prevention before heel lance. The first trial demonstrated a significant reduction of pain score PIPP (Premature Infant Pain Profile) [13], one of these showed a reduction of pain score NIPS (Neonatal Infant Pain Scale) and crying duration [14], one illustrated a reduced cry and treatment duration [15], one showed no effect concerning NIPS [16], and the latest trial demonstrated significantly higher PIPP scores only with NESAP (noninvasive stimulation of acupuncture points) and lower PIPP scores with NESAP combined with sucrose solution [17]. The most frequently used acupuncture point in these trials was Large Intestine 4 (Abbreviation: LI 4, in Chinese: He Gu) [10–13].

Therefore, the aim of this trial is to investigate the effect of laser acupuncture at LI 4 for pain prevention in healthy term neonates undergoing minor painful interventions compared to standard care with orally administrated glucose solution.

## 2. Methods

### 2.1. Design

This study is designed as a single centre, observer-blinded, noninferiority, randomised, clinical controlled trial with two study arms, started on 14 March 2016, and collected data until the end of 2016. This trial is performed at the Division of Neonatology, Department of Paediatrics and Adolescent Medicine, Medical University of Graz, Austria, Europe.

This trial is registered in German Clinical Trials Register with the registry number DRKS00010122 on 2 March 2016.

### 2.2. Participant Enrolment and Eligibility Criteria

We will enrol and include healthy term neonates (>37 weeks' gestational age) without clinical and/or congenital complications, after spontaneous delivery or Caesarean section, receiving heel lance for metabolic screening between 2nd and 5th day postnatally and with written informed consent signed by the parents.

The participants will not be enrolled or be excluded, if there will be lack of written informed consent or current pain therapy in the neonate and/or in the breastfeeding mother. We will not enrol preterm neonates (<37 weeks' gestational age), neonates with clinical and/or congenital diseases, and neonates who are not receiving heel lance for metabolic screening.

Parents of neonates matching the inclusion criteria will be informed about the trial on the first days after delivery. To guarantee achieving adequate participant enrolment, the nursing staff at Department of Obstetrics and Gynaecology, Medical University of Graz, will be informed about the course of the study, and informational conversation with parents will be held daily. After requiring a signed written informed consent, the participant data will be collected and the heel lance will be performed from a medical doctor at the Division of Neonatology in a special treatment room.

### 2.3. Participants

This study will include 95 healthy term neonates during their hospitalisation after delivery. Using the Randomizer for Clinical Trials tool (https://www.randomizer.at/) developed at the Medical University of Graz, neonates will be allocated into one of two groups. One group is the intervention group and will receive laser acupuncture at acupuncture point LI 4 bilaterally (acupuncture group = AG). The other group is the active control group and will receive standard care treatment with orally administered glucose solution (glucose group = GG).

### 2.4. Intervention

Before the procedure starts, participants will be randomised in AG or in GG. Neonates in both groups will be monitored with a pulse oximeter (IntelliVue X2, Philips Medicin System, Boeblingen GmbH, Boeblingen, Germany) across the right wrist to observe heart rate and peripheral oxygen saturation during the intervention and the blood sampling. In addition, neonates in both groups will wear an eye protector (Natus Biliband Eye Protector, Natus Medical, San Carlos, California) during the treatment with laser acupuncture or oral glucose solution, following the same treatment protocol so that all participants will be manipulated equally. The eye protector will be removed 30 seconds before the heel lance.

*AG*. Participants will receive laser acupuncture at LI 4 bilaterally, 60 seconds at the left point and 60 seconds at the right point, in total 120 seconds. 30 seconds until heel lance are left.

*GG*. Neonates in this group will receive orally administered glucose solution for 30 seconds and two minutes waiting period until heel lance.

The intervention in both groups will take in total 150 seconds. Afterwards, the standardised process of blood sampling with heel lance will be carried out.

The complete procedure of blood sampling will be recorded on video, excluding the intervention with laser acupuncture or oral glucose solution. The video will start 15 seconds before heel lance and will record until blood sampling is completed. These video recordings will be analysed by a certified paediatric nurse, who will determine the PIPP for each neonate, blinded to group allocation. To improve the adherence to the study protocol a medical doctor is following written standards of procedure (SOP).

Figure 1 shows the time schedule of enrolment and assessments and Figure 2 gives information about the study course.

### 2.5. Outcome Measurement

The primary outcome is the mean difference in PIPP score between AG and GG.

Secondary outcomes will be mean differences in heart rate change from baseline, in oxygen saturation change from baseline, and in crying time, as well as any adverse events during intervention.

Explorative outcome parameters will be general behavioural state (sleeping, awake, agitated, or crying) of the neonate before intervention, the last breastfeeding time point before intervention, and the number of heel lances performed that will be notated. The duration of blood sampling will be recorded in seconds.

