### 2.7. Premature Infant Pain Profile (PIPP)

The PIPP score is a possibility to evaluate acute pain intensity and is largely used and validated for preterm and term neonates during a painful intervention [20, 21]. Ballantyne et al. demonstrated a good construct validity, differentiating pain from nonpain and baseline events (*F* = 48, *p* = 0.0001), as well as interrater reliability (reliability coefficients of 0.93–0.96) and intrarater reliability (reliability coefficients at 0.94–0.98) for pain assessment in preterm and term neonates [22].

The following indicators will be evaluated: (1) gestational age, (2) behavioural state before painful stimulus, (3) change in heart rate during painful stimulus, (4) change in oxygen saturation during painful stimulus, (5) brow bulge during painful stimulus, (6) eye squeeze during painful stimulus, and (7) nasolabial furrow during painful stimulus.

In each category 0 to 3 points can be allocated. Conversely, point 1, gestational age, and point 2, behavioural state before painful stimulus, have a reversed score (3, 2, 1, and 0) accounting for physiological differences related to prematurity.

The maximum PIPP score for preterm < 28 weeks' gestational age is 21 points and 18 points for term neonates. Accordingly, the number of achieved points on the PIPP score is directly proportional to the neonate's pain intensity during the painful intervention.

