### 2.15. Sample Size

In a group of neonates receiving laser acupuncture, Gottschling et al. reported a pain reaction following heel lance of 6.4 ± 1.9 in PIPP score [13]. Assuming a SD (standard deviation) of 1.9 in pain scores of neonates undergoing heel lance, a sample size of 95 neonates will have a power of 80% (one-sided *t*-test) to reject the null hypothesis that the laser acupuncture and oral glucose administration are not equivalent (the difference in means, *μ*AG  −  *μ*GG, is 1.0 or farther from zero in the same direction) in favour of the alternative hypothesis that the means of the two groups are equivalent, assuming that the expected difference in means is 0. Assuming a minimal dropout of *n* = 5 neonates, we expect to include 95 participants in total.

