### 2.16. Statistical Analysis

We will compare the PIPP scores of both groups using intention-to-treat analysis (ITT). Furthermore, per-protocol (PP) analysis will be performed, since ITT analysis increases the chance of finding noninferiority (increase of type I error) [29]. Results of ITT and PP analysis will be compared.

First baseline characteristics of both groups (gestational age, sex, APGAR score, birth weight, birth size, head circumference, birth mode, and day of life at the time of heel lance) will be compared using *t*-test or Mann–Whitney *U* test for continuous variables and chi-square test or Fisher's exact test as appropriate. For differences in these characteristics, further analysis will be adjusted.

Laser acupuncture will be considered noninferior to oral glucose administration, if the upper boundary of the two-sided 95% confidence interval (CI) for the mean difference between laser acupuncture and oral glucose administration will be less than the margin, *δ* = 1. If data will not be normally distributed, nonparametric tests will be applied.

For ITT analysis, missing primary outcome measures will be imputed by using multiple imputations. For PP analysis, no imputations will be performed. Secondary outcomes will be compared using *t*-test or Mann–Whitney *U* test for continuous variables and chi-square test or Fisher's exact test as appropriate. Since interventions will be of short duration and no risks are associated with the intervention, no interim analysis will be performed.

The used statistic programs for statistical analysis will be IBM SPSS Statistics (Statistical Package for the Social Sciences) and SAS (state-of-the-art statistical analysis software).

The primary outcome measure is the PIPP score as defined above.

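### Behavioural state and last feed before treatment are listed as outcomes and excluded from the PIPP adjustment rule; they belong in the plan as timed, prespecified baseline covariates, for a gain that may be small

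*Protocol article*

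**What the plan says.** Section 2.5 of the protocol article states: "Explorative outcome parameters will be general behavioural state (sleeping, awake, agitated, or crying) of the neonate before intervention". The same sentence adds "the last breastfeeding time point before intervention" and the number of heel lances, and the next sentence adds the duration of blood sampling. The list therefore mixes two things known beforehand with two that arise during the procedure.

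Section 2.16 names the characteristics to be compared between groups: "gestational age, sex, APGAR score, birth weight, birth size, head circumference, birth mode, and day of life at the time of heel lance". It then gives the adjustment rule: "For differences in these characteristics, further analysis will be adjusted". State and last feed are not among the eight, and no covariate is fixed unconditionally for PIPP.

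Section 2.7 lists the PIPP indicators, including "2) behavioural state before painful stimulus", which is reverse-scored. Section 2.4 fixes when the scored recording begins: "The video will start 15 seconds before heel lance and will record until blood sampling is completed".

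**The concern.** A variable fixed before treatment cannot respond to it, so calling it an outcome is a misclassification. The label has a consequence because section 2.16 closes the list of variables that may be adjusted for. A group difference in head circumference would trigger adjustment of the PIPP comparison. A difference in how many babies were crying before treatment, or in time since the last feed, would not. Randomisation is unstratified (section 2.12), so the design does not balance these factors either.

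The timing is also loosely worded. In section 2.4 the intervention is the 150-second treatment period. The title of section 2.6 applies the word to the heel lance, and section 2.8 places the glucose 150 seconds before the intervention, which must again mean the lance. A state recorded before the intervention in that second sense could be recorded after laser or glucose had been given. It would then be a post-treatment measurement and unsuitable as a covariate.

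At stake is precision in the primary comparison, and a clean distinction between a baseline measure and a component of the outcome.

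**Working it through.** **Inputs.** From the article: SD 1.9, margin 1.0, expected difference 0, a one-sided t-test with 80% power, 95 neonates including 5 dropouts (section 2.15); 1:1 allocation (section 2.12); noninferiority judged by the upper limit of a two-sided 95% confidence interval, that is one-sided 2.5% (section 2.16). The SD is stated as: "Assuming a SD (standard deviation) of 1.9 in pain scores of neonates undergoing heel lance". Assumed: the R-squared of the two covariates with PIPP, which the article does not give; the range 0 to 0.30 is shown.

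**Step 1: the plan's own figure.** n per arm = 2·SD²·(z₁₋α + z₀.₈)²/margin².
- One-sided α = 0.05: 2 × 3.61 × (1.645 + 0.842)² = 44.6, so 45 per arm, 90 in total, plus 5 = 95. This reproduces the stated size.
- One-sided α = 0.025: 2 × 3.61 × (1.960 + 0.842)² = 56.7, so 57 per arm, 114 in total, plus 5 = 119. This does not.

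**Step 2: unadjusted power under the stated decision rule.** With 45 per arm, SE = 1.9 × √(2/45) = 0.4006 and the noncentrality is 1/0.4006 = 2.497. With 88 df and one-sided 2.5%, noncentral-t power is 69.5%.

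**Step 3: power with the two covariates.** The model spends 4 df: three for the four-level state and one for time since feed. Two quantities change.
- The residual SD becomes 1.9 × √(1 − R²).
- The variance of the treatment effect is inflated by the expected chance imbalance in the covariates, about 1 + 4/83 = 1.048.

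So SE = 1.9 × √(1 − R²) × √(2/45) × √1.048, with 84 df.

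| Assumed R² | Residual SD | Power | Change from 69.5% (points) |
|---|---|---|---|
| 0 | 1.900 | 67.4% | −2.1 |
| 0.05 | 1.852 | 69.6% | +0.1 |
| 0.10 | 1.802 | 71.9% | +2.4 |
| 0.20 | 1.699 | 76.9% | +7.4 |
| 0.30 | 1.590 | 82.1% | +12.6 |

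Break-even is at an R-squared of about 0.05. Reaching 80% takes a value between 0.20 and 0.30.

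**Step 4: what the inflation term does.** Shrinking the SD and charging only the 4 df gives 71.6%, 73.9%, 78.8% and 83.9% at R-squared 0.05, 0.10, 0.20 and 0.30. The table is therefore about 2 points lower at each value, and that difference removes the apparent gain at 0.05.

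**Step 5: two different measurements of state.** The state in section 2.5, read as before treatment, precedes the 150-second period of section 2.4. PIPP is scored from a recording that starts 15 seconds before the lance, near the end of that period and after the laser or glucose has been given. The state scored as PIPP item 2 is thus post-treatment and part of the outcome. Only the first measurement can be a covariate.

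**The case against.** The strongest reply is that little in the primary inference is wrong. An unadjusted randomised comparison is unbiased, and its confidence interval already allows for chance imbalance. Section 2.16 plans no test of the exploratory parameters, so the label alone alters no result. Covariate choice is often left to an analysis plan, which is not shown. Section 2.4 defines the intervention as the treatment period, which makes the pre-treatment reading of section 2.5 the natural one, and Figure 1, not available here, may settle the timing.

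Much of this stands. No bias is claimed, and the timing point is a request for explicit wording. The appeal to an analysis plan is weaker: the article does not defer the covariates but names a list and a rule, and that rule both excludes these two variables and depends on the observed data.

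A reader might infer that adjustment would recover much of the power shortfall. The article does not support that. It gives no R-squared for either variable. That state is a PIPP item does not show that the pre-treatment state is prognostic, because the scored item is the later, post-treatment state. The item is also reverse-scored and may run against the facial and physiological items, so even the direction of association with the total is unknown. Nothing in the article links last feed to PIPP.

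A reader might also attribute the roughly 70% power to the missing covariates. It comes from a separate mismatch: 95 is reproduced with one-sided 5%, while the decision uses a two-sided 95% interval.

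**Conclusion.** The point holds as a misclassification and as a poorly chosen adjustment rule. Read as before treatment, two baseline variables are called outcomes, and the stated rule keeps both out of the PIPP analysis while admitting eight others on the strength of observed differences. The time at which state is recorded needs explicit wording.

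The effect on power is uncertain in size and can be negative. With 90 evaluable neonates, SD 1.9, a true difference of 0 and 4 covariate df, it runs from a loss of about 2 points at R-squared 0 to a gain of about 13 points at 0.30, with no material gain at 0.05. Prespecification is worth making because the data are already to be collected and it replaces a data-driven rule. It should be presented as an efficiency measure conditional on R-squared, and as neither the correction of a bias nor the answer to the alpha mismatch.

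**What to change.** 1. In section 2.5, move behavioural state and time since last feed from the exploratory outcomes to the baseline variables.
2. State that both are recorded before the allocation is displayed, and use separate words for the study treatment and the heel lance throughout.
3. In section 2.16, prespecify both as covariates in the primary PIPP analysis regardless of observed imbalance, in place of adjustment triggered by differences. Keep state to few categories to limit the df spent.
4. State that the state scored as PIPP item 2 will not be used as a covariate.
5. Describe any power gain as dependent on an unknown R-squared, and separately reconcile the alpha in section 2.15 with the 95% interval rule. Without adjustment, 80% power under that rule needs 114 evaluable neonates (119 with 5 dropouts).

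Cost: wording, up to 4 df, and about 2 points of power if the covariates prove uninformative. No new data items are needed, only a fixed time for recording them.

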### 2.6. Minor Painful Intervention

In this study, all participants will receive a heel lance by automatic lancet (gentleheel®, Alleset Healthcare Solutions B.V., Netherlands) as a routinely used painful minor intervention for blood sampling for metabolic screening [18]. The National Austria Newborn Screening Program started in 1966 and identifies inherited metabolic and endocrine disorders, which every newborn in Austria receives between 2nd and 5th day of life [19].

Before the heel lance, the skin of the newborn will be prepared using a disinfectant (kodan® forte farblos, Schülke & Mayr GmbH, Norderstedt, Germany) and cellulose swabs (Profümed®, Profümed GmbH, Grimmenstein, Austria).

### 2.7. Premature Infant Pain Profile (PIPP)

The PIPP score is a possibility to evaluate acute pain intensity and is largely used and validated for preterm and term neonates during a painful intervention [20, 21]. Ballantyne et al. demonstrated a good construct validity, differentiating pain from nonpain and baseline events (*F* = 48, *p* = 0.0001), as well as interrater reliability (reliability coefficients of 0.93–0.96) and intrarater reliability (reliability coefficients at 0.94–0.98) for pain assessment in preterm and term neonates [22].

The following indicators will be evaluated: (1) gestational age, (2) behavioural state before painful stimulus, (3) change in heart rate during painful stimulus, (4) change in oxygen saturation during painful stimulus, (5) brow bulge during painful stimulus, (6) eye squeeze during painful stimulus, and (7) nasolabial furrow during painful stimulus.

In each category 0 to 3 points can be allocated. Conversely, point 1, gestational age, and point 2, behavioural state before painful stimulus, have a reversed score (3, 2, 1, and 0) accounting for physiological differences related to prematurity.

The maximum PIPP score for preterm < 28 weeks' gestational age is 21 points and 18 points for term neonates. Accordingly, the number of achieved points on the PIPP score is directly proportional to the neonate's pain intensity during the painful intervention.

